#### Strategies to improve adherence to interventions

Efforts will be made in this study to facilitate the ease of access to MedSafer reports and to iteratively improve the MedRec workflow through weekly “plan, do, study, act” cycles. To begin with, an introductory email will be sent to the nephrologists attending on the intervention unit. This email will contain an overview of the study, how it integrates with the existing workflow, and the expectations for the treating nephrologist (to review the MedSafer report at the time of performing a MedRec, perform any relevant deprescribing, provide the deprescribing brochures to the patient, and make a note in the electronic when the MedRec is complete). The study lead will generate sample MedSafer reports for the clinical team, so they can familiarize themselves with the report format prior to the intervention commencing. A physician nephrologist champion ([name]) will be available to answer any questions or concerns.

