### Outcomes

The *primary outcome* will be the efficacy of MedSafer for deprescribing, based on the proportion of patients with 1 or more PIMs deprescribed, compared between the intervention and control units. This will be conditioned on patients with 1 or more PIMs at baseline. Deprescribing will be defined as any PIM that is identified by the MedSafer deprescribing algorithms, that is: stopped or deliberately reduced or tapered.

The key *secondary outcomes* will be the reduction in the mean number of prescribed drugs from baseline following a MedRec compared between the intervention and control units, and implementation barriers and facilitators collected from qualitative, semi-structured interviews with nephrologists on the intervention unit. The number of gastrointestinal bleeds will be reported in total and by intervention status.

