### Who Will Be Blinded?

Clinicians at the control unit will not receive MedSafer reports but will carry out a biannual MedRec as part of usual care. Clinicians rounding on the intervention unit will be made aware of the intervention approximately 2 weeks prior to starting, to allow for familiarization of the MedSafer reports. Four nephrologists will round on the intervention unit during this time, and 3 different nephrologists will round on the control. There is no crossover between physician schedules. Therefore, there is little risk of contamination of the intervention and the control site.

The *Procedure for unblinding* is not applicable to this study.

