## Data Collection and Management

### Plans for Assessment and Collection of Outcomes

Baseline demographic data, the best possible medication history data, the most recent glycated hemoglobin as a measure of diabetes control, and creatinine will be collected for both the control and intervention unit from the electronic medical record (EMR), called NephroCare. These data will be input in the MedSafer web-based portal, and deprescribing reports will be generated for patients on the intervention unit.

Following a MedRec, medication changes will be captured from NephroCare and input into the MedSafer software for both the intervention and control units, permitting an analysis comparing deprescribing that took place on the 2 units.

At the time of MedRec, nephrologists will review the medication list of the patient (obtained from the EMR), validate the list with the patient, and then deprescribe when deemed appropriate (based on the MedSafer report). Medication changes will be faxed the same day to patient’s pharmacy. During this process, if a patient advises the clinical team that they are no longer taking a prescribed drug, this medication will be removed from the patient’s medication list in the EMR. If it is discovered that a patient has already discontinued a drug at the time of performing a MedRec, this will not be counted in the primary outcome of deprescribing.

At the end of the intervention, nephrologists who participated in MedRecs will be invited to participate in semi-structured interviews with the study lead to address their perceived facilitators and barriers related to deprescribing on the dialysis unit. Afterward, themes will be developed from the data collection, according to the grounded theory in qualitative research.^
34
^

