### Data Management

Manual baseline data entry for all patients will occur in the MedSafer web-based portal with data extracted from the NephroCare EMR by a trained study investigator. Any medication changes that occur are input into NephroCare at the time of performing the MedRec. When a MedRec occurs, the date is noted in the unit “task binder” located on site and accessible to all clinicians. MedRecs are considered up to date if they have been completed in the past 6 months and are only redone in the event a patient is hospitalized.

Before and after the MedRecs have been completed, each patient’s medication and comorbidity data will be updated in MedSafer, and a pre- and post-intervention medication dataset (coded by study ID) will be extracted and stored on a secure server. Analysis will be conducted on these coded datasets to record medication changes and deprescribing.

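### The primary outcome depends on judging intent and prior discontinuation, which the before/after medication lists cannot show, and no masking of that judgement is described

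*Protocol article*

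**What the plan says.** The *Outcomes* section of the protocol article defines the event at patient level: at least one PIM flagged by the MedSafer algorithms that is "stopped or deliberately reduced or tapered". *Plans for Assessment and Collection of Outcomes* adds an exclusion: "If it is discovered that a patient has already discontinued a drug at the time of performing a MedRec, this will not be counted" towards the primary outcome. The same section says that such a drug is deleted from the electronic list: "During this process, if a patient advises the clinical team that they are no longer taking a prescribed drug, this medication will be removed".

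The source is common to both units: "medication changes will be captured from NephroCare and input into the MedSafer software for both the intervention and control units". *Data Management* describes baseline entry "with data extracted from the NephroCare EMR by a trained study investigator", followed by extraction of pre- and post-MedRec medication datasets identified by study ID: "Analysis will be conducted on these coded datasets to record medication changes and deprescribing".

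*Who Will Be Blinded?* deals only with clinicians; for the control unit it says "Clinicians at the control unit will not receive MedSafer reports but will carry out a biannual MedRec as part of usual care". It does not mention whoever classifies the outcome. Under *Intervention description*, the study lead enters patient data into MedSafer, generates the reports, and briefs the intervention physicians by email and in person. The study lead also conducts the later interviews with the nephrologists.

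**The concern.** Two judgements sit inside the primary outcome. A lower dose is an event only if it was intended. A drug that disappears from the list is an event only if the patient had not already stopped it. Neither can be read from a list before and a list after, because a PIM stopped by the team and one stopped earlier by the patient both appear as present, then absent. As described, the datasets hold medications and comorbidities, with nothing on who made a change or why.

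The decision must therefore draw on other evidence. No rule for it is given, and the only people described as handling the data are study staff who are not said to be masked to unit. If ambiguous changes are resolved differently on the two units, the estimated risk difference shifts by the net difference in misclassified patients. The planned adjustment for comorbidity index, number of medications and number of PIMs uses baseline covariates and does not correct error in the outcome.

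**Working it through.** **Inputs.** From *Sample Size*: 85 intervention and 153 control patients, about 90% with a PIM (N = 214), 10% control rate, two-sided alpha 0.05, 80% power, about 1:2 allocation, detectable increase 15 points. The documents give no misclassification rate, so the rates below are assumptions, shown as a range.

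**Analysable patients.** 0.9 × 85 = 76.5 and 0.9 × 153 = 137.7; total 214.2. I use 76 and 138.

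**The plan's own figure.** For two proportions with pooled variance under the null and no continuity correction,

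power = Φ[(p1 − p2 − 1.96·s0) / s1], with s0 = √[p̄(1 − p̄)(1/n1 + 1/n2)] and s1 = √[p1(1 − p1)/n1 + p2(1 − p2)/n2].

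For 25% versus 10%: p̄ = (76 × 0.25 + 138 × 0.10)/214 = 0.153; s0 = 0.0515; s1 = 0.0559; power = Φ(0.88) = 81.1%. The detectable difference at 80% power is 14.7 points. With an exact 1:2 split (71 and 143), power is 80.2% and the detectable difference is 15.0 points. The stated figure reproduces.

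**Weight of one patient.** 1/76 = 1.3 points on the intervention unit; 1/138 = 0.7 points on the control unit.

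**Assumed over-counting.** The same formula with 76 and 138 patients. In the middle column the true rate is 10% on both units and only the intervention rate is inflated. In the right column the true rates are 25% and 10% and only the control rate is inflated.

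| Over-count (points) | False result favouring the intervention, over-count on intervention unit | Power, over-count on control unit |
|---|---|---|
| 0 | 2.5% | 81.1% |
| 2 | 7.0% | 67.5% |
| 3 | 10.6% | 59.8% |
| 5 | 20.2% | 44.0% |
| 10 | 53.2% | 13.8% |

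Example for 5 points on the intervention unit: p̄ = (76 × 0.15 + 138 × 0.10)/214 = 0.118; s0 = 0.0460; s1 = 0.0483; (0.05 − 1.96 × 0.0460)/0.0483 = −0.83; Φ(−0.83) = 20.2%.

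In patients, 2 to 5 points is 0.02 × 76 = 1.5 to 0.05 × 76 = 3.8 on the intervention unit, and 0.02 × 138 = 2.8 to 0.05 × 138 = 6.9 on the control unit.

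**Limit of the calculation.** It is an unadjusted comparison of two proportions, as in the plan's sample size, not the planned mixed-effects model. It shows sensitivity to ascertainment error and does not estimate the error.

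**The case against.** The strongest reply is that much of the process is already common to both units and limits the room for judgement. Changes come from one electronic record and go into one software tool. PIM status is set by algorithm. Under *Intervention description*, the nurse checks the list with patient and pharmacy before the study lead enters it, so many self-stopped drugs should be gone before baseline. The outcome is per patient, so a misjudged drug matters only if no other PIM was deprescribed in that patient. All of this stands. It confines the problem mainly to dose reductions and to discontinuations that surface at the MedRec itself. It does not remove it, because the exclusion is written for exactly those late disclosures. Coding by study ID does not settle it either: changes are captured and entered before the coded dataset is extracted.

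It can also be said that a condensed article leaves classification rules to a fuller document. That would answer a complaint about missing detail. Here the stated rule cannot be applied from the stated datasets.

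A reader might go further and infer that records are fuller on the intervention unit, so that detection is biased in its favour. Intervention physicians have a checklist and are asked to "make a note in the electronic when the MedRec is complete", and neither is described for the control unit. The documents do not support that inference. The note is described only as marking completion, not as giving reasons. The checklist is in a supplement that is not shown, and nothing makes it outcome evidence. The direction is also open. Unrecorded intent on the control unit would lose true events there and favour the intervention; unrecorded self-discontinuation there would count list clean-up as deprescribing and favour the control.

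A reader might likewise put the bias at about 8 points, from four patients misclassified on each unit in opposite directions (4/76 + 4/138 = 5.3 + 2.9). That is correct arithmetic on counts that no document supplies.

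**Conclusion.** The point holds as a risk: the primary outcome is open to differential ascertainment of uncertain direction and unknown size. It rests on three features of the text: an outcome rule that needs intent and prior discontinuation, lists in which the competing explanations look alike, and no described masking of whoever decides. It assumes that the datasets carry no reason-for-change field, since none is described, and that the unseen supplement does not supply one for both units.

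The size can only be bracketed. A net error of about two to four intervention patients, if there is no true effect, would raise the chance of a false favourable result from 2.5% to between 7% and 20%. A net error of about three to seven control patients, if the planned effect is real, would cut power from 81% to between 68% and 44%. The protocol should be changed on this point, because the correction is cheap and bears on the primary result. It does not show that the trial's result will be biased towards either unit.

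**What to change.** 1. At the MedRec, record in the same NephroCare entry on both units, for each PIM removed or reduced, whether the team stopped or reduced it or the patient had already discontinued it. Accept this from whichever team member learns of it. Restricting it to the nurse's earlier check would conflict with the plan's own exclusion, which covers disclosures made during the MedRec, and could create false events.
2. Do not use materials that exist only on the intervention unit (report, checklist, completion note) as outcome evidence.
3. Have an existing investigator who takes no part in delivering the intervention classify events from the coded extracts with the unit label removed, under one written rule.
4. Keep the current definition under *Outcomes* as primary. Add a sensitivity analysis counting every baseline PIM stopped or reduced, regardless of judged intent. It will include some incidental changes, so it supports the primary analysis and does not replace it.

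The cost is one extra field in the MedRec entry and a little more data preparation and analysis. No additional patients or staff are needed, and the sample size is unchanged.

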### Participant Timeline

See Figure 1.

**Figure 1. fig1-20543581231165712:**
[figure not shown]
Participant timeline during the study.

### Sample Size

The sample size is fixed to the number of patients in each of the dialysis units (85 patients on the intervention unit and 153 on the control unit). A previous study of MedSafer in hemodialysis estimated ~90% of dialysis patients are prescribed 1 or more PIMs, which is the assumption we will make here as well (N = 214). In our acute care study, we found a baseline rate of PIM deprescribing in the hemodialysis subpopulation of 19.3%. However, in outpatients, deprescribing of sedative hypnotics is often as low as 5%.^
27
^ Therefore, we will estimate a 10% baseline rate of deprescribing. With a 2-sided alpha of 0.05, 80% power, and approximately 1:2 allocation between intervention and control, we can show an increase of at least 15% in the proportion of patients with 1 or more PIMs deprescribed. The statistical code for this calculation is available in the Supplemental Appendix.

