The usual MedRec process occurs as follows: a dialysis nurse first validates with the patient their list of usual home medications and correlates this with the medication list provided by the pharmacy. Discrepancies between the patient’s medication list and the pharmacy’s medication list are resolved through discussion with the patient and pharmacy. Afterward, the treating nephrologist and the nurse review the patient’s list of medications and perform any necessary adjustments. The process is meant to avoid medication duplication, ensure appropriate dosing in the dialysis context, and avoid omissions. Deprescribing does not routinely take place as part of the MedRec process despite this being an opportune time to re-evaluate the ongoing necessity, harms, and benefits of PIMs. Currently, whether deprescribing occurs is nephrologist dependent.

Next, for the purpose of the study, the study lead ([name]) will enter the best medication history (described above), medications, and select laboratory values (hemoglobin A1c and serum creatinine) into MedSafer and generate reports for all patients in the study. The intervention unit (Lachine Hospital) will perform one of their usual biannual MedRecs paired with MedSafer deprescribing reports, including dialysis-specific deprescribing opportunities (the intervention). Reports will be pre-generated and provided to the interdisciplinary team, along with patient deprescribing empowerment brochures.

One of the deprescribing brochures will be a fact sheet on the topic of deprescribing, and others are given for select classes of medications (sedative-hypnotic drugs,^
29
^ gabapentinoids,^
30
^ proton-pump inhibitors [PPIs],^
31
^ and opioids for chronic non-cancer pain^
32
^). The control hemodialysis unit (Montreal General Hospital) will, concurrently, perform their usual biannual MedRec, in the absence of deprescribing reports or patient empowerment brochures.

MedSafer contains deprescribing opportunities from several existing guidelines for safer prescribing in older adults.^18,19,33^ As previously mentioned, the reports will be printed and placed in a study binder at the physician’s desk on the intervention unit and organized alphabetically according to the first letter of the last name of each patient. If MedSafer does not emit any recommendations, a report stating “no deprescribing opportunities were identified at this time” will be generated and placed in the binder.

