### Recruitment

A waiver of consent was granted by the McGill University Health Centre Director of Professional Services for this Quality Improvement Intervention. For the purposes of analysis, only the initial closed cohort will be included in the study. New patients who are initiated on maintenance hemodialysis during the study will not be included. Patients who die or are transplanted prior to a MedRec, or who are admitted to hospital and cannot have a MedRec performed, will be accounted for, described, but excluded from the final analysis.

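### The 80% power for a 15-point increase treats patients as independent, although seven prescribers nested within arm decide the outcome

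*Protocol article*

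**What the plan says.** The Sample Size section takes the two unit rosters as fixed, "85 patients on the intervention unit and 153 on the control unit". It applies a 90% prevalence of at least one PIM, "which is the assumption we will make here as well (N = 214"). It sets a 10% control rate, between 19.3% in the acute-care hemodialysis subgroup and a lower outpatient figure ("in outpatients, deprescribing of sedative hypnotics is often as low as 5"%). For a two-sided test at 5%, power of 80% and roughly one intervention patient to two controls, the section concludes: "we can show an increase of at least 15% in the proportion of patients with 1 or more PIMs deprescribed". No ICC, design effect or attrition allowance is mentioned. The code is in a supplement that is not shown.

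Three other sections bear on this:

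- Intervention description, on the usual MedRec: "Currently, whether deprescribing occurs is nephrologist dependent".
- Who Will Be Blinded?: "Four nephrologists will round on the intervention unit during this time, and 3 different nephrologists will round on the control", with no crossover of schedules.
- Recruitment: patients who die, are transplanted or are hospitalized before a MedRec are "excluded from the final analysis".

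**The concern.** The primary outcome is a prescriber's decision, and the protocol says that this decision varies by prescriber in usual care. Each nephrologist works in one arm only, so differences between nephrologists enter the intervention contrast directly and do not cancel. A power figure for independent patients then overstates what the study can detect.

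The cohort is fixed, so the figure does not set recruitment. It does tell readers how much a non-significant result would mean. Background and Rationale reports a 9.4-point effect in dialysis patients (95% CI 1.3 to 17.6), from acute illness and before dialysis-specific rules were added. The stated 15 points already lies in the upper part of that interval. If the true detectable difference is larger, a non-significant result says less about a 15-point effect than the paragraph implies.

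**Working it through.** **Inputs from the protocol.** Two-sided alpha 0.05; control rate 10%; intervention rate 10% + 15 points = 25%; 0.90 × 85 = 76.5 and 0.90 × 153 = 137.7, taken as 76 and 138 (total 214); four intervention and three control nephrologists.

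**Assumed, because the protocol gives no value.** The ICC within nephrologist; equal loads of 76/4 = 19 and 138/3 = 46 patients; the share of patients excluded.

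**Formula.** Power = Φ[(d − 1.96·s0)/s1], where d is the difference, s0 = √[p̄(1 − p̄)(1/n_C + 1/n_I)] with p̄ the pooled rate, and s1 = √[p_C(1 − p_C)/n_C + p_I(1 − p_I)/n_I].

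**Step 1: reproduce the stated figure.** With n_C = 138 and n_I = 76:

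- p̄ = (13.8 + 19.0)/214 = 0.1533; s0 = 0.0515; s1 = 0.0559.
- (0.15 − 1.96 × 0.0515)/0.0559 = 0.88, so power is 81.1%. The difference detectable with 80% power is 14.7 points.
- At an exact 2:1 split, power is 80.2%, and the required total is 142 + 71 = 213, against 214 stated.
- Other tests at 76 and 138 give 79.2% (Fisher exact), 82.5% (uncorrected chi-square, exact power) and 76.2% (continuity-corrected chi-square).

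The stated figure is therefore correct for independent patients with no exclusions.

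**Step 2: add clustering by nephrologist.** Design effect = 1 + (m − 1) × ICC, so 1 + 45 × ICC for control and 1 + 18 × ICC for intervention. Divide each sample size by its design effect and repeat Step 1.

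| Assumed ICC | Design effect, control / intervention | Effective n, control / intervention | Power, 10% vs 25% | Detectable difference (points) |
|---|---|---|---|---|
| 0 | 1 / 1 | 138 / 76 | 81% | 14.7 |
| 0.005 | 1.225 / 1.09 | 112.7 / 69.7 | 76% | 16.0 |
| 0.01 | 1.45 / 1.18 | 95.2 / 64.4 | 71% | 17.2 |
| 0.02 | 1.90 / 1.36 | 72.6 / 55.9 | 62% | 19.5 |
| 0.05 | 3.25 / 1.90 | 42.5 / 40.0 | 44% | 25.4 |

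At an ICC of 0.001 the effective sizes are 138/1.045 = 132.1 and 76/1.018 = 74.7, and power is 80.0%. There is almost no slack. The normal approximation is also optimistic with only seven clusters.

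**Step 3: exclusions alone (rate assumed).** A 5% loss leaves 131.1 and 72.2 patients: power 79%, detectable difference 15.2 points. A 10% loss leaves 124.2 and 68.4: 77% and 15.7 points. A 5% loss with ICC 0.01 gives 69% and 17.6 points.

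**Step 4: control rate alone (138 and 76, independent patients).** At 5%, power for 15 points is 90.5% and the detectable difference 12.1 points. At 19.3%, they are 68% and 17.7 points.

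**The case against.** The strongest reply is that the arithmetic is right and that the clustering loss rests on a number the protocol never gives. Calling deprescribing nephrologist dependent describes current practice and supplies no correlation. The protocol says that nephrologists round on the units, not that each patient has one responsible prescriber or that loads are equal. Statistical Methods describes the mixed model as controlling for unit, so it does not show that clustering by nephrologist was foreseen. The planned adjustment for comorbidity, medications and PIMs could absorb some of the correlation. All of this stands as a limit on the size of the loss. It does not rescue the stated power, because even a very small positive ICC uses up the one-point margin.

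A reader might go further and infer that the protocol also contradicts the 10% control rate and the full N of 214, so that all three assumptions fail. The documents do not support that.

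- **Control rate.** The 10% lies between two cited figures and has a stated reason, and the Intervention description says that deprescribing is not routine in MedRecs. A lower rate would raise power. It is true that the 5% concerns one drug class while the endpoint is any PIM, but turning that into a patient-level rate needs PIM counts and independence between drugs that the protocol does not give.
- **Exclusions.** They are not deducted from 214, but the retention section and the Discussion expect little loss over two months, and 5% to 10% costs only a few points of power.

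Nor does any passage say that a null result would be taken to rule out a 15-point effect. That is a risk for readers, not a stated plan.

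**Conclusion.** The concern holds for clustering. The 80% power at 15 points is a best case with respect to independence and exclusions, and the design lacks that power for any appreciable correlation within nephrologist. Under assumed ICCs of 0.005 to 0.05 and equal loads, power is about 76% down to 44%, and the detectable difference about 16 to 25 points. The direction is firm because it follows from the protocol's own account of prescribers. The size is conditional on those assumptions.

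Exclusions add little. The control rate is a sensitivity that works in both directions, not an error. With one unit per arm, unit-level variation is confounded with the intervention. The figures above do not cover it, and no sample-size adjustment can remove it.

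**What to change.** Keep the fixed sample and rewrite the closing sentences of the Sample Size section to:

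1. State that 15 points from a 10% control rate is the detectable difference for independent patients and no exclusions, and is a best case on both.
2. Give the detectable difference over a stated ICC range by nephrologist, such as 0.005 to 0.05 (about 16 to 25 points), labelling the range and the equal loads as assumptions.
3. Add control rates from 5% to 19.3% as sensitivity (12.1 to 17.7 points under independence), with one line on exclusions.
4. Note that variation between the two units is confounded with the intervention and lies outside these figures.
5. Say that the result will be interpreted through its confidence interval.

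The cost is one rewritten paragraph with a short table and a less favourable headline figure. No patients or procedures change.
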